## Abstract

**Background:**

Improvement of coordination of all health and social care actors in the patient pathways is an important issue in many countries. Health Information (HI) technology has been considered as a potentially effective answer to this issue. The French Health Ministry first funded the development of five TSN (“Territoire de Soins Numérique”/Digital health territories) projects, aiming at improving healthcare coordination and access to information for healthcare providers, patients and the population, and at improving healthcare professionals work organization. The French Health Ministry then launched a call for grant to fund one research project consisting in evaluating the TSN projects implementation and impact and in developing a model for HI technology evaluation.

**Methods:**

EvaTSN is mainly based on a controlled before-after study design. Data collection covers three periods: before TSN program implementation, during early TSN program implementation and at late TSN program implementation, in the five TSN projects’ territories and in five comparison territories. Three populations will be considered: “TSN-targeted people” (healthcare system users and people having characteristics targeted by the TSN projects), “TSN patient users” (people included in TSN experimentations or using particular services) and “TSN professional users” (healthcare professionals involved in TSN projects). Several samples will be made in each population depending on the objective, axis and stage of the study.

Four types of data sources are considered: 1) extractions from the French National Heath Insurance Database (SNIIRAM) and the French Autonomy Personalized Allowance database, 2) Ad hoc surveys collecting information on knowledge of TSN projects, TSN program use, ease of use, satisfaction and understanding, TSN pathway experience and appropriateness of hospital admissions, 3) qualitative analyses using semi-directive interviews and focus groups and document analyses and 4) extractions of TSN implementation indicators from TSN program database.

**Discussion:**

EvaTSN is a challenging French national project for the production of evidenced-based information on HI technologies impact and on the context and conditions of their effectiveness and efficiency. We will be able to support health care management in order to implement HI technologies. We will also be able to produce an evaluation toolkit for HI technology evaluation.

**Trial registration:**

ClinicalTrials.gov ID: NCT02837406, 08/18/2016.

## Background

### The challenges of Health Information Technologies to improve healthcare coordination

All the health systems face challenges in delivering high-quality, effective and safe care at an affordable cost. Improvement of coordination of all health and social care actors in the patient pathways is an important issue in many countries [1–3]. Healthcare coordination is defined by the Agency for Healthcare Research and Quality as “the deliberate organization of patient care activities between two or more participants (including the patient) involved in a patient’s care to facilitate the appropriate delivery of health care services” [4]. Care coordination is thus the patient-centred organization of care that providers (including patient caregivers) should share to improve the quality of a patient’s management and, ultimately, the patient’s health [5–8]. The development of ambulatory care and the scattering of healthcare producers lead to increasing risk of care fragmentation [9]. Moreover, in the context of the increase in life expectancy and of the number of patients with chronic illnesses, continuity of care becomes a crucial condition for care quality and security [10, 11]. A key success factor to care coordination is sharing of the same holistic view of a patient’s condition by all actors of hospital, ambulatory and medico-social sectors, including the patient’s active diseases and current treatments, and the planned care pathway that establishes the role of each provider. Unfortunately, transitions from one setting or provider to another still frequently lack clear communication and coordination, resulting in an increase in healthcare costs and reduced quality of care including polypharmacy and adverse drug interactions, duplication of services, unnecessary emergency department utilization, high hospital readmissions rates, and in the worst cases patient injury [5, 9, 12, 13].

Given the large volume of transactions in the system and the need for new evidence-based practice and other information management activities, Health Information (HI) technology has been considered as a potentially effective answer to this issue [12, 14]. A recent WHO (World Health Organization) report shows that there is around Europe tangible progress in the mainstreaming of technology solutions to improve public health and health service delivery [15]. At the core of this technology-led transition is an adjustment in the way health information is captured, viewed, processed, exchanged and stored. HI technology involves a broad group of activities that use electronic means to deliver social and health-related information, resources and services.

HI technologies are potentially effective tools to improve information system between healthcare and social care professionals and between patients and health care professionals, allowing a better access to more precise information, improving communication and coordination between healthcare and social care organizations and healthcare professionals. They may allow the centralisation of all patient management information, the creation of shared tools for healthcare coordination, the creation of alerts, feedback, reminders thus favouring the implication of health and social care professionals and patients in their care pathway, continuous quality assessment and care efficiency as well as the development of a shared culture between professionals [15].

Literature on HI technology efficacy and efficiency shows controversial results. Even if many studies show a real but modest effect [16–20], others suggest the absence of positive effect, particularly on outcomes and cost-effectiveness indicators [17, 21–23], acknowledging a gap between the postulated and empirically demonstrated benefits of HI technologies [21, 24]. Some studies even indicate potential risks and unintended effects [25, 26].

These controversial results are explained by methodological reasons (global poor quality of the studies, heterogeneity of evaluated HI technologies and of HI technologies implementation's context, hampering the external validity of the studies) but also by pitfalls in HI technology development, often disregarding the interdependencies between technology, human characteristics and the socioeconomic environment [27–31]. Many researchers advocate larger, well-designed, controlled studies evaluating HI technology against a comprehensive set of measures, ideally throughout all stages of the technology’s life cycle [32, 33]. Such evaluation should be characterised by careful attention to socio-technical factors and organizational issues to maximise the likelihood of successful implementation and adoption [25, 26]. Another key issue for the development of HI technology is the political commitment, backed by sustainable funding. Published evidence of the information needed to make decisions about acquiring and implementing HI technology in different settings is nearly inexistent [15].

### Healthcare coordination and HI technology development in France

In France, rules have been developed since the late 1990s to introduce healthcare system change for healthcare coordination improvement [34]. General Practitioners (GPs) have gained a major role in care coordination, thanks to a semi gate-keeping system that provides incentives to people to visit their GP prior to consulting a specialist. A coordinated care pathway was implemented with higher co-insurance for patients consuming care out of this pathway and new categories of co-payment for patients were created with the introduction of deductibles on some categories of care such as drugs, physicians and nurses consultations or patient transportation. Creation of primary healthcare centres that bring together professionals from different specialties is encouraged to improve coordination of care and cooperation between healthcare professionals. However, major problems include a lack of coordination between hospital and ambulatory services, between private and public provision of care and between healthcare and public health [34].

In this context, French public authorities are supporting HI technologies development. In 2014, a governmental grant, called TSN (“Territoire de Soins Numérique”/Digital health territories), selected five HI technology development projects across five pilot areas containing between 200,000 and 500,000 inhabitants each in five French regions: Aquitaine, Bourgogne, Ile-de-France, la Réunion and Rhônes-Alpes. These HI technology projects are supposed to introduce changes in healthcare organization, aiming at improving healthcare coordination and access to information for healthcare providers, patients or the population and at improving healthcare professionals’ work organization.

In September 2014, the French Health Ministry launched a call for grant to fund one project that should develop a method to evaluate the five TSN projects’ use and implementation and their impact on three main outcomes: healthcare quality, healthcare professionals’ work organization and efficiency. The selected project should also be able to create a general framework for the evaluation of HI technology services.

### The EvaTSN project

This article presents the protocol of the project that was selected, called EvaTSN (Evaluation Territoire de Soins Numérique). It has been conceived by a multidisciplinary team composed of health services researchers, economists, sociologists, management researchers, HI technology researchers, epidemiologists and healthcare professionals. An operational team is in charge of the project lead and management.

The project’s main objectives consist in evaluating the TSN program implementation and impact and developing a model for HI technology evaluation. The specific objectives are structured around four axes: 1) TSN program implementation and use; 2) Impact of TSN program on patient pathway quality and safety, including access to care; 3) Impact of TSN program on healthcare professionals work organization; and 4) Economic sustainability and efficiency of the TSN program.

## Methods

### Design of the study

The study is mainly based on a controlled before-after study design (Fig. 1). Data collection covers periods before TSN program implementation (2012-2015 or T0 period), during early TSN program implementation (2016, T1 period) and at late TSN program implementation (starting in 2017, T2 period), in the five TSN projects territories and in five comparison territories. Analyses of TSN program implementation and use are based on a before-after design.

**Fig. 1 Fig1:**
[figure not shown]
EvaTSN project data collection schedule and organization, France

### The interventions – the TSN projects

All the TSN projects develop digital services for healthcare users and healthcare and social care producers (hospitals, ambulatory sector, medico-social sector) to improve healthcare coordination, collaboration between professionals and access to healthcare and prevention information and professional guidelines (Table 1).

**Table 1 Tab1:** Presentation of digital/E-services and functionalities in each TSN project area – EvaTSN project, France

Type of E Health Services	E Health-services functionalities	AQT	BGN	IF	LR	RHA
Organisation of healthcare coordination^a^	- Platform for service coordination	✓	✓	✓	✓	✓
	- Digital coordination service	✓	✓	✓	✓	✓
	- Call center for informal caregivers					✓
E-services for users/patients	- Diffusion service of general healthcare information	✓	✓	✓	✓	✓
	- Medical information management services	✓	✓	✓	✓	✓
	- Administrative information management services	✓	✓	✓	✓	✓
	- Community of connected patients				✓	
E-services for professionals	- General health information service	✓	✓	✓	✓	✓
	- Professionals' patient medical information management	✓	✓	✓	✓	✓
	- Administrative information management services	✓	✓	✓	✓	✓
	- Community of connected professionals		✓	✓		✓
Administrative and monitoring services for policy makers	- Administrative monitoring	✓	✓	✓	✓	✓
	- Epidemiological monitoring		✓		✓	✓
	- eHealth innovation promotion	✓	✓	✓	✓	✓
	- Interoperability management	✓	✓	✓	✓	✓

^a^between healthcare producers and between health care producers and patients, *AQT* aquitaine, *BGN* Bourgogne, *IF* Ile-deFrance, *LR* La Réunion, *RHA* Rhône-Alpes

Most TSN projects target patients with chronic conditions or elderly dependent people. Some of them focus on patients suffering from specific diseases, including congestive heart failure (Aquitaine, Bourgogne, la Réunion regions), cancer (Bourgogne, Ile-de-France regions), stroke (Bourgogne), respiratory failure (Aquitaine), or specific populations, including young people (Bourgogne), pregnant women (Ile-de-France), obese and disabled people (la Réunion), and situations of social vulnerability (Bourgogne, Ile de France).

### Study populations

Three populations will be considered: 1) “TSN targeted people”: healthcare system users and people having characteristics targeted by the TSN projects, 2) “TSN patient users” that is to say people included in TSN experimentations or using particular services and 3) “TSN professional users”, i.e. healthcare professionals involved in TSN projects. Several samples will be constituted in each population depending on the objective, axis and stage of the study.

### Outcomes and measurements – data sources and data collection

Four types of data sources are considered (Table 2).

**Table 2 Tab2:** EvaTSN project data collection: indicators collected, data collection tools and study populations, France

Assessment/Indicators	Study populations	Type of data collection	Data collection tool
Axis 1 – TSN projects implementation			
Knowledge of TSN projects	HS^d^ users	Ad hoc survey	Ad hoc questionnaire
TSN program use and understanding	TSN users	Ad hoc survey	Ad hoc questionnaire
TSN implementation and development indicators	TSN users	IS^a^ Extraction	TSN programs ID^b^
TSN implementation, barriers and facilitating factors	TSN implementers & stakeholders	Qualitative analyse	Semi-structured interviews
Axis 2 – TSN projects effectiveness on pathway quality			
Prevalence of hospital admissions appropriateness	HS^d^ users	Ad hoc survey	AEPf questionnaire
Number of per day hospital emergency entries	HS users	IS Extraction	SNIIRAM^c^
Prevalence of drug over- or misuse in the elderly	HS users	IS Extraction	SNIIRAM
Potentially avoidable hospitalizations	HS users	IS Extraction	SNIIRAM
Prevalence of chronic diseases	HS users	IS Extraction	SNIIRAM
Incidence of chronic diseases	HS users	IS Extraction	SNIIRAM
Incidence of disorders reflecting management pathway breaks	HS users	IS Extraction	SNIIRAM
30-day hospital readmission rate after a first hospital admission	HS users	IS Extraction	SNIIRAM
TSN use satisfaction and TSN pathway experience	TSN users	Ad hoc survey	Ad hoc questionnaire
Perception of TSN pathway contribution to patient pathway	TSN users	Qualitative analyse	Semi-structured interviews
Axe 3 – TSN projects effectiveness on professional coordination practices			
GPs’ activity volume	HS users	IS Extraction	SNIIRAM
Percentage of home visits in GPs’ activity	HS users	IS Extraction	SNIIRAM
Percentage of patients with GP noted as referent in GPs’ patient list	HS users	IS Extraction	SNIIRAM
GPs’ productivity (activity/estimated hours available)	HS users	IS Extraction	SNIIRAM
Percentage of patients with chronic conditions in GPs’ patient list	HS users	IS Extraction	SNIIRAM
Mean duration between two consecutive consultations of a same patient	HS users	IS Extraction	SNIIRAM
Percentage of night and bank holiday home visits in GPs’ activity	HS users	IS Extraction	SNIIRAM
Number of prescriptions of nursing care or physiotherapy in GPs’ activity	HS users	IS Extraction	SNIIRAM
Health professionals’ coordination practices	Health care prof users	Qualitative analyse	Semi-structured interviews
Health professionals’ participation level to TSN program	Health care prof users	Qualitative analyse	Semi-structured interviews
Axe 4 – TSN programs efficiency			
Health care expenditures (all types)	HS users	IS Extraction	SNIIRAM
Incidence of APA^1^ take-up Annual rate of institutionalization in APA beneficiaries originally living at home	HS users	IS Extraction	SNIIRAM
Hours of home helper visits done in people with APA living at home	HS users	IS Extraction	SNIIRAM
Average level of co-payment amongst APA beneficiaries living at home	HS users	IS Extraction	SNIIRAM
Health prevention expenditures	HS users	IS Extraction	SNIIRAM

^a^Information system, ^b^TSN program Information Database, ^c^SNIIRAM: French National Heath Insurance Database, ^d^Health system, ^1^APA is a personalized Autonomy allowance for the elderly, granted to cover home-care, nursing-care or institutional-care expenses

Extractions from the French National Heath Insurance Database (SNIIRAM) will be conducted to collect the main set of indicators for axes 2, 3 and 4. This exhaustive nationwide database is at the heart of the financing system of diagnosis, drugs and physicians in ambulatory care settings and of independent practitioners in private hospitals (essentially fee for service). It provides data on claims paid for each patient by the Social Security System and is therefore the main source of information on ambulatory setting activity and associated expenditures. This database contains patient data (age, sex, place of living, long-term and chronic diseases, date of birth, date of death, health insurance scheme, benefit of free complementary insurance for lower-income people), all consultations and visits to GPs and ambulatory care specialists (but nothing about their content), all medical technical procedures, all dispensed medical devices and drugs, all lab and diagnostic tests but not their results, and providers’ level data (their activity and sales turnover, geography, prescribing behaviour). This database is also linked with the PMSI (programme de médicalisation du système d’information/Information system medicalization program) database providing more detailed information on hospital activity and expenditure, including diagnoses and procedures. Extractions from the SNIIRAM will cover the time period from 2012 to 2017 and will focus on samples from the “TSN targeted people” population, in both TSN projects and control areas. Data will also be extracted from the APA (Allocation personnalisée d’autonomie/personalized autonomy allowance) database. APA is a financial support for the elderly to cover home-care, nursing-care or institutional-care expenses.

Ad hoc surveys based on questionnaires will collect information on:Knowledge of TSN projects assessed at T1 (early-implementation observation) and T2 (late-implementation observation) in a sample of the “TSN targeted people” population (axis 1);TSN program use, ease of use, satisfaction and understanding assessed at T2 in a sample of the “TSN professional users” population (axis 3);TSN use satisfaction and TSN pathway experience assessed at T2 in a sample of the “TSN patient users” population (axis 2);Appropriateness of hospital admissions assessed using the validated French version of the Appropriateness Evaluation Protocol questionnaire (AEP) in most emergency services of the TSN and control areas, twice, before TSN program implementation (T0) and at early TSN program implementation (T1) (axis 2). The survey will be carried out by one clinical research assistant assessing the appropriateness of hospital admissions of the same week day for each TSN project area and its control area.

Qualitative analyses using semi-directive interviews and focus groups will be conducted in the five TSN project areas by a team of sociologists. Three samples will be included: a sample of around 50 TSN professional users interviewed at T0, T1 and T2, for the exploration of professionals’ coordination practices, their evolution and the level of TSN projects use and adoption by professionals (axis 3); based on a biographical approach (*Illness narrative*), a sample of 10 TSN projects patients-users interviewed monthly after TSN project implementation for the exploration of users’ participation to TSN projects and the analysis of the TSN program’s contribution to patient pathway (axis 2); and a sample of the TSN national program and the five TSN projects developers and main stakeholders interviewed at T1 to analyse the way projects have been implemented, what worked well and their barriers and difficulties. Patients, TSN professionals and TSN project developers will receive incentives for their participation to qualitative analyses. The sample size of 3 × 50 participants have been decided to favor heterogeneity of health-care professionals recruited. At each step (T1, T2 and T3), 50 health-care professionals will be recruited from the five TSN territories and from the five health- and social-care professional categories: general practitioner, private-sector specialist physician, private-sector nurse, physicians working at hospital, social care professional. Sample should also be heterogeneous according to TSN program implication.

A set of standardised TSN implementation indicators will be requested to TSN projects producers and extracted from each TSN project’s database.

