### Control territories

Each control territory is chosen to be as similar as possible to each corresponding TSN project territory, based on simple quantitative indicators. The identification method has already been used in France for the evaluation of another public policy (implementation of a minimal income for low-income people). Each control territory is chosen in the same region as the TSN project territory to control for regional policy effects. It must have roughly the same size as the TSN project territory, be a compact geographical zone and not be too geographically close to the TSN project territory, in order to avoid contamination. The selection process, described elsewhere, is carried in three steps:Constitution of a list of candidate control territories, according to geographic, demographic and healthcare offer criteria;Sorting of the list according to the territory’s structural similarity with the TSN project territory, based on a set of 20 criteria classified in four categories: 1) population demographic characteristics influencing healthcare demand; 2) population social and economic characteristics; 3) population health and 4) healthcare offer. The similarity analysis is based on factorial analyses;Determining the territory that is the most similar to the TSN amongst the subset of candidate territories, according to the number of emergency room visits’ evolution, which is potentially influenced by TSN projects effects. This analysis is based on time series models. Were also considered in the final choice: feasibility of data collection and existence of competitive interventions in the territory.

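### The 30-day readmission indicator is a rate per admission, and TSN may change who is admitted, so the rate can rise while readmissions per targeted person fall; a per-person rate should stand beside it

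*Protocol article*

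**What the plan says.** In the protocol article, Table 2 (Outcomes and measurements) places the "30-day hospital readmission rate after a first hospital admission" under "Axis 2 – TSN projects effectiveness on pathway quality", to be extracted from SNIIRAM. The wording makes it conditional on an index admission. The same block of the table lists "Potentially avoidable hospitalizations" and the daily number of hospital emergency entries.

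The Control territories section describes the trend in emergency room visits as something "which is potentially influenced by TSN projects effects". The Background counts "unnecessary emergency department utilization, high hospital readmissions rates" among the consequences of poor coordination.

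Data analysis and interpretation says that effects are estimated on the whole populations targeted by a service and calls this intention-to-treat. Indicators are directly standardized: by age and sex for general-population measures, and by clinical and social background, as far as that can be done, for measures in particular groups. The article does not discuss selection into admission and does not say how the readmission rate is to be read against the admission indicators.

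**The concern.** A rate per admission compares people who were admitted after TSN began with people who were admitted without it. If TSN alters who is admitted, these two groups differ in readmission risk even when the TSN and control territories are perfectly comparable as populations. The comparison then loses the protection of a whole-population estimate, which is what the article says it is making.

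At stake is the direction of the statement about readmissions. A service that prevents some lower-risk stays, and so prevents the readmissions that would have followed them, could be reported as having raised the readmission rate. The report goes to the Health Ministry, and the article hopes to inform policy, so a wrong sign on this indicator would matter.

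**Working it through.** The article gives no readmission rate, risk mix or expected effect, so there is no figure to reproduce. All rates below are assumptions.

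**Set-up.** A fixed targeted population produces 1,000 index stays a year: L = 400 at readmission risk pL = 8%, and H = 600 at pH = 20%. TSN averts a share a of the low-risk stays and changes nothing else.

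Rate per admission = [L(1 − a)pL + H·pH] / [L(1 − a) + H]

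- a = 0: (32 + 120) / 1,000 = 152 / 1,000 = 15.2%
- a = 5%: (30.4 + 120) / 980 = 150.4 / 980 = 15.3%; readmissions change by 150.4/152 − 1 = −1.1%
- a = 50%: (16 + 120) / 800 = 136 / 800 = 17.0%; readmissions change by 136/152 − 1 = −10.5%, the rate by 17.0/15.2 − 1 = +11.8%

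**Why the two measures part.** Readmissions per person = index admissions per person × readmissions per admission. At a = 50% the ratios are 0.80 × 1.118 = 0.895. The conditional rate shows only the second factor.

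**What fixes the direction.** Removing stays whose risk is below the average raises the average, whatever share is removed. Removing stays above the average lowers it. A second assumed set shows this: 30 avoidable stays and 70 others at 20%, with half of the avoidable stays averted (85 stays left).

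| Risk of avoidable stays | Rate before | Rate after | Readmissions before → after |
|---|---|---|---|
| 5% | 15.5% | 17.4% | 15.5 → 14.75 |
| 10% | 17.0% | 18.2% | 17.0 → 15.5 |
| 15% | 18.5% | 19.1% | 18.5 → 16.25 |
| 20% | 20.0% | 20.0% | 20.0 → 17.0 |
| 25% | 21.5% | 20.9% | 21.5 → 17.75 |

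Readmissions fall in every row; the rate rises in three, is flat in one and falls in one.

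**How much true improvement would hide it.** In the first set, a uniform relative cut in risk cancels the rise when it reaches 1 − 15.2/15.35 = 1.0% for a = 5%, and 1 − 15.2/17.0 = 10.6% for a = 50%. Smaller cuts still show as a rise.

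**What standardization could do.** With exact weights on the two strata, the rate after TSN is 0.4 × 8% + 0.6 × 20% = 15.2%, so the spurious rise disappears. That needs strata that capture readmission risk. Age and sex need not do so, and SNIIRAM holds tests but not their results. Even perfect standardization would show no change here and would miss the 152 − 136 = 16 readmissions avoided.

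**The case against.** The strongest reply is that the distortion is probably small. The article describes earlier effects of such technology as modest, analyses whole targeted groups rather than users, expects diluted associations, and warns that not all effects will be visible in time. At 5% of low-risk stays averted the shift is about 0.1 percentage point, and a 1% improvement in risk cancels it. This stands as a limit on size. It does not settle the direction.

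It can also be said that averted stays need not be low-risk, since the targets include heart failure, respiratory failure and dependent elderly people. That is right, and the direction is therefore left open here. Clinical standardization with linked PMSI diagnoses is also foreseen and would help, but the article commits to it only where feasible. Avoidable hospitalizations and emergency entries are already in the axis, but nothing ties them to the readmission rate.

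Three stronger readings are tempting and are not supported:

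- **That TSN is meant to leave fewer and sicker inpatients.** The article does not say so. Table 2 lists indicators without a direction.
- **That the "Prevalence of hospital admissions appropriateness" has the same fault.** If the less-needed admissions are averted, that share rises: assuming 75 of 100 appropriate and half of the other 25 averted, 75 / 87.5 = 85.7%. It would fall only if appropriate admissions dropped proportionally more, for example by being sent directly to wards, and the article describes no such route.
- **That the whole Axis 2 conclusion could have the wrong sign.** The article names no primary or composite outcome for the axis, so the risk is confined to the statement about readmissions.

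**Conclusion.** The point holds for the 30-day readmission rate alone. The indicator conditions on an event that TSN may change, which fits poorly with the stated whole-population estimate. It can move against, or ahead of, the change in readmissions per targeted person. In the assumed example the rate goes from 15.2% to between 15.3% (5% of low-risk stays averted) and 17.0% (50% averted), while readmissions fall by 1.1% to 10.5%. The upper figure needs a large effect on admissions. The upward direction requires that averted stays carry below-average readmission risk, with little change in risk within strata. None of these inputs comes from the article, so the real size is unknown.

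**What to change.** Keep the conditional rate and estimate two companions beside it, TSN versus control, in the same targeted group: 30-day readmissions per 1,000 targeted people per year, and index admissions per 1,000 targeted people per year. State that any conclusion about the effect on readmissions rests on the per-person and per-admission figures read together. Define the targeted group so that membership does not depend on being admitted in the same year, or the denominator problem returns.

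The cost is small. The SNIIRAM extraction with its PMSI link already covers targeted-group samples in both kinds of territory from 2012 to 2017, so this is extra tabulation and no new data collection. The downside is that a per-person rate mixes admission volume with quality of care after discharge. For that reason it should not replace the conditional rate.

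No matching change is proposed for the appropriateness survey. It is run "in most emergency services of the TSN and control areas", and the article does not say that those assessed are all area residents, so a count per resident would have a mismatched numerator and denominator.
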